#### Preprocessing

Bandpass filtering is applied to the signals to remove high-frequency interference. A combination of empirical mode decomposition and wavelet transform is used to filter out baseline drift and physiological interference in the signals. A correlation-based signal improvement algorithm is employed to remove motion interference from the signals. Data is segmented according to the position of the target stimulus.

#### fNIRS signal feature extraction and modeling

Sensitive channel selection: This is done by calculating the classification accuracy rates of HbO, Hb, and THb for each channel, and accumulating these rates to amplify differences; channels are selected based on the changes in amplitude of the HbO, Hb, and tHb signals during the acquisition process.

Feature extraction and modeling from sensitive channels: Several features are extracted from the three hemodynamic signals of HbO, Hb, and tHb (the sum of HbO and Hb signals) in the sensitive channels. A support vector machine (SVM) classifier is used to establish a classification recognition model. The features that the recognition model can use mainly include mean values, fitted slopes, and approximate entropy.

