### The process of fNIRS gage and record analysis

Our experiment’s FNIRS gage apparatus, the ETG-4000 (Hitachi Ltd., Japan), uses two wavelengths of near-infrared light (695 and 830 nm) to find differences in oxygenated hemoglobin (HbO), deoxygenated hemoglobin (HbR), and total hemoglobin (HbT). Hemoglobin variations may be monitored 2–3 cm below the surface, which corresponds to the brain’s cortex, using 3 cm between the source and the detector. The measurements will be conducted using a 52-channel fNIRS device. This system includes 33 probes (17 emitters and 16 detectors) arranged in a 3 × 11 configuration fixed to the scalp, in accordance with the international 10–20 system (33). Measurement channels are established between each emitter-detector pair, producing a total of 52 channels. See Figure 5 for the channels. The fNIRS probes will include the frontal skin and superior temporal skin. Upon stabilization of the probes, the signal power of every channel. Will be assessed. Signals from channels may be influenced by the cleanliness of the probes and obstructions, like as pile, between the probes and the scalp. Consequently, if the signal intensity of a channel is determined to be inadequate, prompt actions like scalp cleansing, probe adjustment, and hair repositioning will be implemented.

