### Outcome measures

Clinical Results: Clinical result metrics encompass the Tinnitus Handicap Inventory (THI), ABR testing, and fNIRS data collection. Evaluations will be carried out at baseline, after 10 treatment sessions.

THI score: The THI is a self-reported checklist that’s quick, simple. To manage and interpret, and covers a wide range of issues. It consists of 25 items, each scored from 0 to 4. An elevated THI indicates a more severe level of tinnitus.

ABR testing: The test records the peak latencies (PL), wave amplitudes, and interpeak intervals (IPL) of the subjects at various stimulation rates, as well as the differences in PL and IPL at the two stimulation rates (ΔPL and ΔIPL) to evaluate the function of the peripheral auditory nerve.

fNIRS data acquisition and processing: Cortical blood oxygen data will be collected to evaluate the central function of the subjects.

fNIRS results: fNIRS scans will be conducted at baseline, and after 10 treatment sessions. The blood oxygen concentrations measured include the concentrations of oxygenated hemoglobin (HbO), hemoglobin that has lost oxygen (HHb), and total hemoglobin (THb) in every measured channel.

fNIRS functional connectivity intensity: The intensity of functional connectivity between regions can quantify the relationships between routes or areas of interest within the fNIRS time plots. This is computed using the Pearson correlation coefficient between the average time series of any pair of channels of interest. The functional connectivity strength between channels of interest, as well as between channels of interest and other channels, is computed using NIRSKIT software. This software will help in analyzing the correlation between the time series data from different channels, providing insights into the connectivity patterns within the brain that may be associated with tinnitus and its treatment.

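### fNIRS channels are screened by classification accuracy before an SVM is built on them, with unnamed classes and no stated separation of selection from evaluation; reusing subjects and labels would bias SVM accuracy upward

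*Protocol article*

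**What the plan says.** The relevant text is in the protocol article, section on fNIRS signal feature extraction and modeling. It sets out a screen followed by a model.

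- Screen: sensitive channels are found by "calculating the classification accuracy rates of HbO, Hb, and THb for each channel, and accumulating these rates to amplify differences".
- The same sentence continues with another rule: "channels are selected based on the changes in amplitude of the HbO, Hb, and tHb signals during the acquisition process". How the two rules combine is not explained.
- Model: "Several features are extracted from the three hemodynamic signals of HbO, Hb, and tHb (the sum of HbO and Hb signals) in the sensitive channels". Then "A support vector machine (SVM) classifier is used to establish a classification recognition model". The usable features "mainly include mean values, fitted slopes, and approximate entropy".

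The classes to be told apart are not named. The Preprocessing section, just before, says "Data is segmented according to the position of the target stimulus". The montage is described as "producing a total of 52 channels". Study design gives one pool of subjects: 72 patients randomised 1:1, plus 15 healthy volunteers.

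Outcome measures lists blood-oxygen concentrations for every channel measured. It also plans connectivity, described as "The functional connectivity strength between channels of interest, as well as between channels of interest and other channels", without defining the channels of interest. Analytical statistics plans t-tests on the fNIRS data, permutation tests and FDR correction. It ties none of these to the channel screen or to the SVM.

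**The concern.** A screen that ranks channels by how well they classify uses the class labels. If the SVM is then trained and scored on the same subjects with the same labels, the labels have been used twice. Among 52 channels some will separate the classes by chance. The screen keeps those, and the SVM is credited with the separation. Adding up the accuracies of three signals brings little independent information, since the article defines total hemoglobin as the sum of the other two.

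Cross-validation added after the screen does not cure this, because the held-out subjects already helped to choose the channels. The order of the steps is itself the problem.

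At stake is how any reported classifier accuracy can be read. The Discussion says the study aims to supply objective ways of assessing acupuncture's effect on tinnitus, and the Introduction puts fNIRS forward, with ABR, for that gap. An accuracy clearly above chance with no true difference would lend that aim false support.

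**Working it through.** The article gives no accuracy, validation scheme or error rate for the screen or the SVM, so there is no figure of its own to reproduce. The check is a simulation with no true difference between classes.

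**Inputs from the article.** 52 channels; 3 signals, the third being the sum of the first two; 3 feature types. This gives 52 × 3 × 3 = 468 candidate values per subject. Class sizes tried: 36 v 36 (randomised), 30 v 30 (the calculated requirement per group) and 72 v 15 (patients v healthy).

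**Assumptions not in the article.** The classes are study groups. Features are Gaussian. Between-channel correlation is 0 or 0.5. The best 5 or 10 channels are kept. The screen uses each signal's 5-fold accuracy (nearest centroid), summed over the three signals. The amplitude criterion is not applied.

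**Steps.** In each of 300 null datasets per setting, rank the channels, keep the best, and fit a linear SVM on their HbO and Hb features (the third signal is redundant). Score by balanced accuracy = ½(proportion correct in class 1 + proportion correct in class 2), so chance is 50% even for 72 v 15. Three scores are taken: on the training data (resubstitution), by 5-fold cross-validation after selection on all subjects, and by 5-fold cross-validation with selection repeated in each training fold (nested).

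**Mean accuracy (%) under no effect**

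| Classes | Correlation | Kept | Resubstitution | CV after selection | Nested CV |
|---|---|---|---|---|---|
| 36 v 36 | 0 | 5 | 90.0 | 62.3 | 50.8 |
| 36 v 36 | 0 | 10 | 100.0 | 63.6 | 50.1 |
| 36 v 36 | 0.5 | 5 | 85.3 | 57.6 | 50.4 |
| 36 v 36 | 0.5 | 10 | 98.9 | 57.5 | 49.4 |
| 30 v 30 | 0 | 5 | 95.1 | 62.4 | 50.0 |
| 30 v 30 | 0 | 10 | 100.0 | 64.7 | 50.3 |
| 30 v 30 | 0.5 | 5 | 90.2 | 58.6 | 50.5 |
| 30 v 30 | 0.5 | 10 | 99.9 | 58.4 | 50.2 |
| 72 v 15 | 0 | 5 | 96.2 | 63.9 | 50.5 |
| 72 v 15 | 0 | 10 | 100.0 | 64.5 | 50.1 |
| 72 v 15 | 0.5 | 5 | 92.9 | 58.3 | 50.2 |
| 72 v 15 | 0.5 | 10 | 99.1 | 58.1 | 49.5 |

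The simulation standard error of the cross-validated figures is 0.4-0.5 percentage points. The excess over chance when cross-validation follows selection runs from 57.5 − 50 = 7.5 to 64.7 − 50 = 14.7 points. A separate null simulation (correlation 0.3, 10-fold, linear and radial SVMs) gave 60-65% after selection and 49-51% nested.

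**What the resubstitution column means.** It is mostly ordinary overfitting. Here 5 or 10 channels give 5 × 2 × 3 = 30 or 10 × 2 × 3 = 60 features, on 60 to 87 subjects. In a null run with correlation 0.3 and all nine features per channel, channels drawn at random, with no selection at all, gave 82-89% (5 channels) and 100% (10 channels). The effect of selection is therefore read from the gap between the last two columns.

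**Group t-tests, conditional case.** The HbO mean was also compared between the classes in the same null datasets.

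| Channels tested | t-tests with p < 0.05 | Datasets with any FDR finding |
|---|---|---|
| Only those kept by the screen | 9.7-16.1% | 7.3-27.0% |
| All 52 | 4.6-5.3% | 1.7-7.3% |

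Testing all channels is about nominal. FDR over the kept channels alone does not remove the selection.

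**The case against.** Several points count against a harder reading, and most of them stand.

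- **The classes may not be the treatment groups.** A reader might infer acupuncture v sham, but the article does not say so. Patient v healthy, before v after treatment, and stimulus segments are all possible. With stimulus segments, selection need not bias acupuncture-sham differences. This limits the consequence for group tests but does not rescue SVM accuracy, which is inflated for any labels used both to select and to score.
- **The amplitude-change rule uses no group label.** If it alone decided the channels, label-based selection would not arise. The article states both rules and does not relate them, so this is an ambiguity to settle and not a defence.
- **Reuse of the same subjects is inferred.** A condensed article may leave hold-out or cross-validation to a fuller document, and silence on that would be no finding by itself. But the article does fix an order, accuracy screen first and model second, and describes one pool of subjects. Ordinary cross-validation added to that order still gave 58-65% under no effect.
- **FDR and permutation tests are planned.** They are not linked to the screen. Permutation protects the SVM result only if selection is rerun in every permutation.
- **The classifier is secondary.** SVM accuracy is not listed as an outcome or in Analytical statistics, and nothing says the trial's conclusion rests on it.

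**Conclusion.** The point holds in limited form. Followed as written, with the same subjects and labels in both steps, screening by accuracy and then modelling overstates SVM accuracy. Cross-validation after selection shows about 58-65% where the truth is 50%: 62-65% with uncorrelated channels and 58-59% at correlation 0.5. The size rests on the assumed correlation, number of channels kept, Gaussian features and class definition. The direction was the same in all twelve settings.

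Two stronger inferences are not supported. First, that the acupuncture-sham channel comparisons are biased: this would need tests limited to channels picked by group-label accuracy. The article records every channel, does not equate channels of interest with sensitive channels, and does not restrict the t-tests or FDR. Second, that selection produces the 85-100% resubstitution accuracy: random channels give nearly as much.

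This should be corrected before the data are analysed. It concerns an exploratory classifier, not the comparison of THI scores.

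**What to change.** In the section on fNIRS signal feature extraction and modeling:

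1. Name the classes the SVM is to separate.
2. State how the accuracy and amplitude-change criteria combine, or drop one.
3. Repeat channel and feature selection inside each training fold (nested cross-validation). If a subject contributes several scans or segments, keep them all in one fold.
4. Report only held-out accuracy, with a permutation p-value in which every permutation reruns the whole pipeline, including selection.

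In Outcome measures and Analytical statistics, state that group and connectivity tests use all 52 channels with FDR, or channels of interest fixed on anatomical grounds before unblinding (for example auditory/superior temporal and prefrontal), and never channels picked by group-label accuracy.

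The cost is some extra computing, a few sentences of text, and a reported accuracy that will be lower. No change to recruitment, scanning or treatment is needed.

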### Analytical statistics

Date analysis will be done using SPSS version 26 (IBM Corporation, Armonk, NY, 2019), with a two-sided significance threshold established at 0.05. In terms of data description, continuous data is presented as mean ± standard deviation (x ± s), and categorical and ordinal data is stated as proportions (%). The intervention effects will be represented by OR and 95% CI. Data on immediate and cumulative effects of the two acupuncture groups, clinical scoring, ABR parameter analysis, and fNIRS data analysis is compared using T-tests. Permutation tests will be used, and multiple comparisons will be examined using False Discovery Rate (FDR) correction. The differences in THI scores, ABR parameters, and functional values of brain regions will be analyzed for correlation using Pearson’s correlation analysis, with inspection level *α* = 0.05.

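### The analysis section reports intervention effects as odds ratios, but every stated efficacy outcome is numeric and compared by t-test, so the effect measure fits neither the outcomes nor the test

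*Protocol article*

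**What the plan says.** Outcome measures names the outcome set: "Clinical result metrics encompass the Tinnitus Handicap Inventory (THI), ABR testing, and fNIRS data collection". Each component is numeric:

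- **THI:** "It consists of 25 items, each scored from 0 to 4. An elevated THI indicates a more severe level of tinnitus".
- **ABR:** "The test records the peak latencies (PL), wave amplitudes, and interpeak intervals (IPL) of the subjects at various stimulation rates", plus the changes in latency and interval between the two stimulation rates.
- **fNIRS concentrations:** oxygenated, deoxygenated and total haemoglobin in each channel.
- **fNIRS connectivity:** "This is computed using the Pearson correlation coefficient between the average time series of any pair of channels of interest".

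Analytical statistics describes continuous data by mean and standard deviation, and categorical and ordinal data by proportions. It then says "The intervention effects will be represented by OR and 95% CI". The next sentence says that "clinical scoring, ABR parameter analysis, and fNIRS data analysis is compared using T-tests". Permutation tests, false-discovery-rate correction and Pearson correlation are also named, but no logistic or other odds-ratio model.

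Sample size estimation uses a formula for two population rates, P1 and P2. It gives neither their values nor the event they count, and arrives at 30 per group, raised to 36.

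**The concern.** A t-test asks whether two means differ, and its natural effect estimate is the difference in means with a confidence interval. An odds ratio between arms needs a binary event or an ordinal model. The article pairs t-tests with an odds ratio and states nothing that links them. Followed as written, the p-value would describe one endpoint (mean THI, mean latency) and the reported effect another (some dichotomised or ordered version of it).

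Two things are at stake. First, the two results can disagree for the same data, and the text does not say which one represents the intervention effect. Second, the plan does not commit to an interval for the quantity that its t-tests address: how many THI points, or how many milliseconds of latency, separate acupuncture from sham.

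**Working it through.** **1. Outcomes, test and effect measure side by side**

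| Outcome (Outcome measures) | Scale | Cut-off or event stated? | Test (Analytical statistics) | Matching effect measure | Stated effect measure |
|---|---|---|---|---|---|
| THI | sum of 25 items scored 0 to 4 | no | t-test | mean difference | OR |
| ABR latencies, amplitudes, intervals | continuous | no | t-test | mean difference | OR |
| fNIRS haemoglobin concentrations | continuous | no | t-test | mean difference | OR |
| fNIRS connectivity | correlation coefficient | no | t-test | mean difference | OR |

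In no row does the stated effect measure match the stated test.

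**2. Does the sample-size section supply the missing event?**

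The 30 per group cannot be reproduced, because P1 and P2 are not given. It can be solved backwards. With two-sided alpha 0.05 and 80% power, u_α + u_β = 1.960 + 0.842 = 2.802. The required arcsine difference is 2.802 × √(1641.4/30) = 20.7 degrees. Assumed pairs that give this difference are 20% vs 54%, 30% vs 65% and 50% vs 83%. Over assumed control rates of 10% to 60%, the implied odds ratio is about 4.4 to 6.0. So 30 is attainable for a response rate, but no such rate appears among the outcomes.

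**3. What the same 30 per group means for a t-test**

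By the normal approximation, the detectable standardised difference is 2.802 × √(2/30) = 0.72.

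**4. The odds ratio depends on a cut-point that the article does not state (illustration)**

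Assume a normal outcome and a difference of 0.723 SD. With a control responder rate of 30%, the threshold is 0.524 SD above the control mean. The acupuncture rate is 1 − Φ(0.524 − 0.723) = 0.579, so OR = (0.579/0.421)/(0.30/0.70) = 3.2. Over assumed control rates of 10% to 70%:

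- the OR runs from 3.2 to 3.6;
- power for comparing the two proportions at 30 per arm runs from 45% to 59%;
- 49 to 69 per arm would be needed for 80% power.

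**5. Simulation (illustration)**

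20,000 trials, 30 per arm, SD 1, true difference 0.736 SD. Wald 95% CI for the OR, with a 0.5 correction when a cell is zero. The t-test was significant in 79.8% of trials.

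| Cut-point (SD from control mean) | OR interval excludes 1 | t-test significant, OR interval includes 1 |
|---|---|---|
| −0.5 | 43.3% | 38.0% |
| 0 | 56.7% | 25.1% |
| 0.368 | 62.6% | 19.9% |
| 0.5 | 62.0% | 20.4% |
| 1.0 | 50.8% | 30.7% |

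Only the 30 per arm comes from the article. The effect size, the normal distribution and the cut-points are assumptions. An independent re-run agreed within simulation error.

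**The case against.** **Odds ratios are not confined to binary events.** A proportional-odds model gives one for ordinal data, and the article does mention ordinal data. This stands as a matter of method, so it would be too strong to infer that no odds ratio could ever be formed. But the article names no such model, and its mention of ordinal data is only a rule for description.

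**The odds ratio may be meant for safety.** Evaluation of safety does count adverse events. However, the odds-ratio sentence covers intervention effects without limit, and the safety section names no odds ratio. The support vector machine classifier does not help either: it classifies fNIRS signals and does not define treatment success.

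**A cut-off may sit in the full protocol or the analysis plan.** That is fair, and a missing cut-off alone would be no finding. The point rests on what is stated: an effect measure that does not fit the outcomes and test named beside it.

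**Readers could rebuild the mean difference.** This is largely true. Means and standard deviations are promised, and with the group sizes they give a crude difference and interval. The loss is therefore one of clarity and commitment. The information itself is not lost.

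**The rate-based sample size suggests an intended response rate.** This stands, and it limits the fix: replacing one sentence without looking at that section would leave the rates unmatched.

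**Conclusion.** The point holds as an internal contradiction. The stated effect measure does not correspond to the stated outcomes or the stated test. That conclusion comes from the text alone and needs no assumption.

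The figures show only what dichotomising generally costs: about 43% to 63% of odds-ratio intervals exclude 1, against 80% significance by t-test, under the assumptions listed. They are not an estimate for this trial.

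A reader might infer more in two ways, and the article supports neither:

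- **That a threshold would be picked after the data are seen.** Nothing says so, and a cut-off could be fixed in a document not shown.
- **That the false-positive rate is inflated.** With no true effect, at least one of four cut-points (−0.5, 0, 0.5 and 1.0 SD) gave a significant odds ratio in 12.1% of simulated trials, against 5.2% for the t-test. That applies only if several cut-points were tried and the best kept, which the article does not suggest. In a re-run, a single cut-point gave 2.8% to 5.1%.

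The correction should be made, because it is specific and cheap.

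**What to change.** In Analytical statistics, replace the odds-ratio sentence with text such as:

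> The intervention effect on THI, on each ABR parameter and on each fNIRS measure will be reported as the difference in means (acupuncture minus sham acupuncture) with its 95% CI, from the same analysis that gives the p-value. Odds ratios will be used only for binary outcomes, such as the occurrence of an adverse event.

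Sample size estimation must then be aligned by restating the basis of the 30 per group as a difference in means. By the normal approximation, 30 per group corresponds to about 0.72 SD at 80% power. The article gives nothing from which to judge whether that difference is realistic.

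If a response rate was intended, add the event to Outcome measures, fix its cut-off and time point before unblinding, name a matching binary analysis, and give P1 and P2 for that event. The t-tested outcomes still need mean differences.

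The first route costs one sentence in the analysis section and a rewritten sample-size paragraph, and the change of effect measure needs no new visits or data. Its downside is that the headline effect is no longer a ratio. The second route needs more text, and the sample size must be checked against the stated rates.

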## Materials and methods

### Study design

Our research is structured as a regulated and randomized trial with assessor blinding. Seventy-two participants who qualify with chronic tinnitus will be allocated in a 1:1 ratio to either the acupuncture group or the sham acupuncture group. Additionally, we will recruit 15 healthy individuals as subjects for data collection to compare the auditory brainstem response parameters and extracerebral oxygen levels of the cerebral cortex between chronic tinnitus patients and healthy subjects, and to observe the correlation of peripheral-central auditory function under different physiological states. Our protocol’s reporting complies with the Standard Protocol Items: Recommendations for Interventional Trials (SPIRIT) criteria. The SPIRIT for the study is shown in Figure 1, and the flowchart is shown in Figures 2, 3.

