#### Allocation concealment and randomization

Suitable participants will be assigned at random to the acupuncture group or the sham acupuncture group in a proportion of 1:1 using a random stratification block design by gender and lifetime, with the Statistical Product and Service Solutions Version 25.0 (SPSS Inc., Chicago, IL, USA). An impartial administrator, uninvolved in other study protocols, will conduct this process, and the details of the list of random allocations will remain completely confidential. This randomization results will be preserved in opaque, sealed, envelopes with sequential numbers to guarantee allocation concealment.

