### Sample size estimation

The formula for calculating the two independent sample sizes in Sun Zhenqiu’s “Medical Statistics” is:

$$n=1641.4\times {\left[\frac{\left(u_{a}+u_{\beta }\right)}{\sin^{-1}\sqrt{P_{1}-\sin^{-1}}\sqrt{P_{2}}}\right]}^{2}$$

In the formula, *n* represents the required sample size, the two population rates’ predicted values are, respectively, denoted by P_1_ and P_2_, while u_α_ and u*_β_* are the *u* values according to the exam level *α* and type II error probability *β*, respectively. Assuming *α* = 0.05 and *β* = 0.20, through calculation, the required sample size for each group is 30 cases. Based on a 20% exclusion rate, 36 cases should be included in each group, for a total of 72 patients.

According to the requirements for data analysis in imaging studies, a minimum of 12 healthy subjects should be included. Considering potential uncertainties such as subject head movement during scanning that may render data unusable, to ensure the reliability of data analysis, it is advisable to include 15 healthy subjects.

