
Indeed, the strength of our study stem from its innovativeness. For what I can tell, there has been alone one similar exploration that utilized fNIRS to investigate the neurological processes behind acupuncture in the treatment of tinnitus (27). However, the preceding research, serving as a pilot experiment, included just 18 individuals with tinnitus and lacked a randomized controlled design. Additionally, it focused specifically on HbO2 concentration as the fNIRS-related result. Secondly, in the process of evaluating the efficacy of acupuncture and moxibustion on chronic tinnitus patients, we used ABR as one of the evaluation indicators, which makes our evaluation indicators more objective. In contrast, the objective evaluation indicators for the previous RCT study of acupuncture and moxibustion treatment of chronic tinnitus are not clear. To address these prior shortcomings, our research is structured as a randomized, assessor-blinded controlled experiment. Given the novelty of fNIRS in tinnitus and acupuncture research, our findings are partly expected to shed light on the neural mechanisms underlying the effects of acupuncture on tinnitus. Furthermore, our study aims to provide objective methods for assessing the therapeutic effects of acupuncture on tinnitus.

While our study offers several innovative aspects and methodological strengths, it is not without limitations. Firstly, as a single-center study, the sample size may lack representativeness, which could potentially impact the reliability of the results. Secondly, the severity of tinnitus among participants was not restricted in our study. This variability could influence the outcomes, and therefore, prospective research should seek more participants with similar degrees of tinnitus severity to control for this variable and reduce its potential confounding effects on the study results. Thirdly, due to technical limitations, fNIRS can only measure the hemodynamics and neural activity in the superficial areas of the cerebral cortex, and it cannot capture the activities in deeper brain regions.

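### Arm comparisons are set as t-tests with no baseline or stratum term, which is valid but gives up precision that the collected data could supply

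*Protocol article*

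**What the plan says.** All places are in the protocol article.

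- **Analytical statistics** names the test: "Data on immediate and cumulative effects of the two acupuncture groups, clinical scoring, ABR parameter analysis, and fNIRS data analysis is compared using T-tests". It adds: "Permutation tests will be used, and multiple comparisons will be examined using False Discovery Rate (FDR) correction". It does not say which comparisons the permutation tests serve, or whether they respect the strata. Testing is done "with a two-sided significance threshold established at 0.05". No covariate, stratum term, ANCOVA or mixed model appears in this section or elsewhere in the article.
- **Allocation concealment and randomization** assigns patients 1:1 "using a random stratification block design by gender and lifetime". 'Lifetime' is not defined; age is the likely meaning.
- **Outcome measures** gives the timing for THI, ABR and fNIRS: "Evaluations will be carried out at baseline, after 10 treatment sessions".
- **Discussion** lists as a limitation that "the severity of tinnitus among participants was not restricted in our study", says that this could affect the outcomes, and leaves the remedy to future studies.
- **Sample size estimation** arrives at 30 per group before allowance for exclusions.

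**The concern.** The design gathers two kinds of information that the stated analysis does not use. One is the pre-treatment value of each outcome, which usually predicts the post-treatment value. The other is the set of factors on which the randomisation is balanced. Stratified allocation removes between-stratum variation from the true sampling error of the arm difference. An unadjusted t-test still counts that variation in its standard error.

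A second gap is that the t-test could be run on final values or on changes. With about 30 patients per arm, chance baseline differences can make the two disagree, and the article does not fix which one counts.

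At stake are power and interval width in a small trial that compares deep with shallow needling at the same points and spreads its tests over many ABR and fNIRS measures under FDR control.

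**Working it through.** **The plan's own figure.** The 30 per group comes from an arcsine formula for two rates ("Assuming *α* = 0.05 and *β* = 0.20"). The article prints the rates as symbols only, so 30 cannot be reproduced. Two checks are possible. The constant is right: (180/π)²/2 = 1641.40. And n = 30 corresponds to a standardised effect of √(2/30) × (1.960 + 0.842) = 0.723. I take from the plan only n = 30 evaluable per arm and two-sided α = 0.05.

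**Assumptions not in the documents.** r is the correlation between baseline and post-treatment value, varied from 0.3 to 0.8. Baseline and post-treatment variances are equal and set to 1. The effect is d = 0.723, chosen because it gives a final-value t-test 80% power at 30 per arm.

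**Formulas.** Variance of the analysed quantity:

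- final-value t-test: V = 1
- change-score t-test: V = 2(1 − r)
- ANCOVA on baseline: V = 1 − r²
- ratio of ANCOVA to change score: (1 − r²)/[2(1 − r)] = (1 + r)/2

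Power = Φ(d/√(2V/30) − 1.960). For V = 1: 0.723/0.258 = 2.802, and 2.802 − 1.960 = 0.842, so power is 80%. For ANCOVA at r = 0.5: 2.802/√0.75 = 3.235, and 3.235 − 1.960 = 1.275, so power is 89.9%.

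| r | V, change | V, ANCOVA | Cut vs final | Cut vs change | Power, final | Power, change | Power, ANCOVA |
|---|---|---|---|---|---|---|---|
| 0.3 | 1.40 | 0.91 | 9% | 35% | 80% | 65.8% | 83.6% |
| 0.5 | 1.00 | 0.75 | 25% | 25% | 80% | 80.0% | 89.9% |
| 0.7 | 0.60 | 0.51 | 49% | 15% | 80% | 95.1% | 97.5% |
| 0.8 | 0.40 | 0.36 | 64% | 10% | 80% | 99.3% | 99.7% |

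These are large-sample values. No choice of r makes ANCOVA less precise than either t-test.

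**Effect of the strata.** A simulation used 60 patients, four strata, permuted blocks of 4, within-stratum r = 0.5 and 6,000 runs per scenario. With no treatment effect, the final-value t-test behaved as follows:

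| Outcome variance explained by strata | Mean reported SE | True SE | Type I error |
|---|---|---|---|
| 0% | 0.257 | 0.256 | 4.8% |
| 5% | 0.257 | 0.251 | 4.1% |
| 10% | 0.258 | 0.246 | 4.0% |
| 20% | 0.259 | 0.236 | 3.2% |

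The SE is too large by about 2% (0.257/0.251), 5% (0.258/0.246) and 10% (0.259/0.236) in the last three rows. The model with strata and baseline had type I error of 4.8% to 5.2%.

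**Which part matters more.** With d = 0.723 and strata explaining 10%, simulated power was 79% (final-value t-test), 82% (change-score t-test), 82% (strata only) and 91% (strata and baseline). With strata explaining nothing, the full model still reached 88%, against 79% for both t-tests. Most of the gain therefore comes from baseline, and unneeded stratum terms cost little.

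**The case against.** The strongest reply is that randomisation makes the unadjusted t-test a valid test of the arm effect. That stands. A reader might infer from the ignored strata that the inference is unsound or that false positives rise. The simulation shows the opposite: type I error sits at or below 5%, and the SE excess is negligible if gender and age predict the outcomes weakly.

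A reader might also infer that adjustment would lift power from 80% to 90–98%. That holds only against a final-value t-test with r between 0.5 and 0.7. The article does not specify final values, and its reference to effects and differences fits change scores just as well. Against change scores the gain at r = 0.7 is from 95.1% to 97.5%. Nor is 80% a design figure for a continuous outcome here, since the trial was sized on two rates.

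Three further readings go too far:

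- That severity was left open on purpose: the Discussion only lists it as a limitation.
- That baseline adjustment disposes of the severity problem: adjusting each outcome for its own baseline puts THI severity into the THI model only, and a main effect does not address a treatment response that varies with severity.
- That every arm comparison is an unadjusted t-test: permutation tests are named too, though nothing says that they are stratified or adjusted.

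Finally, this is a condensed article, and a fuller plan may add covariates. That limits certainty about what will be done. It does not remove the point, because the article states a specific method and that statement is what is reviewed here.

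**Conclusion.** The point holds as one of efficiency. The named t-tests are valid and at worst conservative, but they use neither the strata nor, if run on final values, the baseline. If run on changes, they use baseline less efficiently than ANCOVA does. The size of the loss rests on r and on how well the strata predict each outcome. The article gives neither, and both will differ between THI, ABR and fNIRS measures. The gain is modest at one end of the range whichever t-test is meant: at low r against final values, at high r against change scores. Leaving the analysed quantity unstated is a defect in its own right, and naming ANCOVA removes it.

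**What to change.** In Analytical statistics, replace the t-tests for the acupuncture versus sham comparisons by ANCOVA: post-treatment value on arm, baseline value of the same outcome, and the stratification factors actually used. These are gender and age once 'lifetime' is confirmed to mean age; the randomisation section should say so. Report the adjusted mean difference with its 95% CI. Wherever permutation tests compare the arms, permute arm labels within strata.

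The cost is a few sentences. No further patients, visits or measurements are needed, and SPSS, already named, fits the model. The change should be made before unblinding, so that the choice between final values, changes and adjusted values cannot appear to depend on the results.
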